### Arrangements for allocating participants to trial groups

Seven centres across Canada are participating in this trial (London, Calgary, Toronto, Vancouver, Edmonton, New Westminster, Winnipeg). All surgeons (n = 15) have been assigned to a design that will minimize the impact of expertise on study outcomes. Those with > 2 years recent experience in both procedures will require conventional design. Surgeons with primary expertise in only one procedure are paired with those with expertise in the alternative procedure from the same site and subject to expertise-based design. In both designs, the randomization scheme will be stratified by surgeon and compensation status (Workplace Safety and Insurance Board (WSIB), litigation or disability). We will use variable permuted block sizes to randomize patients on a 1:1 ratio; block sizes will remain confidential to the biostatistician to protect the integrity of the randomization scheme. Local research assistants will identify all patients (eligible participants, eligible non-participants and non-eligible), reasons for ineligibility or refusal, and obtain consent from eligible patients.

#### Conventional RCT

Patients will arrive at their surgical consultation where the surgeon will assess patient eligibility during history and physical examination, taking into account diagnostic information provided from pre-consultation MRI. The surgeon will explain the clinical trial and that by agreeing to participate, the patient has a 50:50 chance of receiving either method (mini-open or all-arthroscopic) to repair the torn rotator cuff tendon. The research assistant will obtain informed consent and contact the central randomization computer to obtain patient identification number and treatment assignment.

#### Expertise-based RCT

Patients will arrive at their surgical consultation where the surgeon will assess patient eligibility as per above. If eligible, the surgeon will explain the clinical trial and that by agreeing to participate, the patient has a 50:50 chance of receiving either method (mini-open or all-arthroscopic) to repair the torn rotator cuff tendon and that another surgeon from the same centre may perform the operation depending on group allocation; the surgeon performing the procedure will have expertise in performing that procedure. The research assistant will obtain informed consent and contact the central randomization computer to obtain patient identification number and surgeon (treatment) assignment. Two of the larger centres (Calgary and London) have some surgeons who qualify for the conventional RCT and others (pairs) for the expertise-based RCT so this factor will also be block randomized at these sites.

### Outcome measures

#### Primary outcome

##### Western Ontario Rotator Cuff Index (WORC)

The WORC was developed and validated as a self-report evaluative measure of quality of life specific to patients with rotator cuff disease [48]. The questionnaire consists of 21 items that are organized into five domains including pain and physical symptoms, sports and recreation, work, lifestyle, and emotional well-being. Reproducibility of the WORC has been demonstrated at 2 weeks and 3 months (0.96 and 0.93 respectively) [48]. In addition, this instrument has demonstrated ability to detect change. While studies vary, our recent work suggests that the WORC is more responsive than other scales [49]. All studies agree that the WORC is a valid measure of quality of life in patients experiencing rotator cuff problems when compared to alternative instruments [48,50]. All self-report measures will be administered by a blinded research assistant at each assessment point.

### Secondary outcomes

#### Complications/Cuff integrity

A standardized complications checklist has been developed. This will be used to monitor infection rate and other known post-surgical problems. MRI will be used to detect repair failure at 1 year post-operatively. Examination of the rotator cuff using MRI is highly correlated to surgical findings for full thickness tears, having a sensitivity and specificity of 85% and 83% for first-time shoulder surgery, and 84% and 91% for failed repairs [45]. For the purposes of this study, all MRI series will be reviewed by radiologists with special expertise in musculoskeletal imaging. The radiologists will conduct all measurements from the MRI images and will remain blinded to group allocation. Patients for whom MRI is contraindicated will be examined by ultrasound. Patients will undergo an MRI of the rotator cuff at 12 months post-operatively to evaluate cuff integrity. This is an appropriate time to ascertain whether the repair remains intact, as further biological recovery is unlikely. Cuff failure at this point may require revision surgery. Furthermore, delay of MRI would risk losing this key information if patients are lost to follow-up between the 1 and 2-year time points. Specifically, the MRI will document the size of the defect in the proximal to distal, humeral to bursal, superior to inferior direction in all four tendons, the muscle atrophy using the tangent sign (supraspinatus only), and the degree of fatty infiltration (supraspinatus and infraspinatus) as defined in previous work [7]. The appearance of the biceps tendon and any tear will be described (normal, tendinosis, partial-thickness tear (thinned or longitudinal split), or complete tear) and measured. Changes in the size of tear, muscle atrophy, and degree of fatty infiltration from the pre-operative state will be determined. This procedure has been used in an ongoing trial based at McMaster University and data collection will follow the same standardized format.

#### Self-report

The American Shoulder and Elbow Surgeons shoulder scale (ASES) [51] will provide a secondary measure of shoulder pain and disability; the Work Limitations Questionnaire [41] will measure work difficulties; and the SF-12 [42,52,53] will measure general health status. The ASES was selected as it is used internationally in shoulder studies and will allow comparability of data across trials. It has a single pain item and a 10-item function subscale. The Work Limitations Questionnaire [41] has been used to study loss of occupational productivity in other musculoskeletal disorders [41,54] and we have recently validated it for use in rotator cuff disorders ([name] manuscript in progress). The SF-12 is an abbreviated multi-item general health scale that evaluates the two domains of physical and mental health through summary scores. The SF-12 (version 2) correlates highly with the SF-36 [52,55,56] and has proved valid in a wide variety of populations and contexts. It was selected for this study because it allows a lesser respondent burden which was important given the burden of multiple self-report scales.

#### Physical impairments

##### ROM

A blinded research assistant will assess active and passive measurements of range of motion (ROM), including forward elevation, abduction, and internal and external rotation. These will be measured at all post-operative assessments using a Universal standard goniometer, which is reliable (ICC (range) = 0.85–0.99) for the measurement of shoulder ROM [57,58].

##### Strength

Strength of shoulder flexion, abduction, and internal and external rotation will be measured using a hand-held dynamometer. Patients will be sitting and have the arm placed in a neutral position. Maximum isometric strength will be measured over 3 trials using procedures which are known to produce reliable scores [59-62]. Each of the test sites will be provided a new dynamometer that has been calibrated to ensure validity of obtained measurements.

##### Composite Impairment Score (Constant)

The Constant is a composite summary score which addresses pain, activities of daily living, range of motion, and strength [63-69]. It takes approximately 10 minutes to administer [63]. This is not a self-administered questionnaire; the research assistant must work through each section with the patient [70]. For the purposes of this trial, a differential rate between shoulders will be calculated as it has been shown to provide a more precise estimate of function. In addition, we will use strength measures from dynamometry to provide more accurate estimates of muscular capability than possible with subjective ratings [63].

### Trial measures

We will monitor all aspects of recruitment and protocol compliance between study designs as study outcomes. In addition, we will measure patient and surgeon satisfaction with the study process and patients' proclivity for future trial participation.

#### Proposed methods for protecting against other sources of bias

##### Control over eligibility violations is under review of the central adjudication committee

The Central Adjudication Committee (CAC), blinded to patient group allocation, will review all operative reports and eligibility forms from all randomized patients to ensure they met eligibility criteria. This committee will consist of the principal investigator, an orthopaedic surgeon, and an epidemiologist. Any patient judged to be ineligible by the CAC, according to information available at the time of randomization, will be omitted from the final analysis and the reason for exclusion recorded. This will be recorded as a minor protocol violation.

##### Control of biases through blinding

Surgeons cannot be blinded. However, the patient, the data collector, radiologist, and data analyst are blinded to group allocation for the duration of the study and data analysis. As the primary outcome is self-report, bias is minimized.

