#### Planned trial interventions

This trial compares two different methods of repairing a torn rotator cuff. Patients will undergo either 1) a mini-open repair where the repair is performed though a small incision and the arthroscope can be used to address problems within the joint (as per traditional diagnostic procedures); or 2) an all-arthroscopic procedure where joint techniques and repair are both performed entirely thought the arthroscope. While many surgeons have used arthroscopy for diagnosis and debridement, repair through the arthroscope is substantially different and requires additional training and experience. Thus, these methods are quite distinct to surgeons. JOINTS Canada surgeons have discussed elements of the repair that can be standardized and those that must be left to surgeon preference. A protocol for surgery/rehabilitation has been established for study centres.

a. *Arthroscopic repair *will consist of subacromial decompression, repair of the torn cuff tendon, and debridement of partial (up to 50%) tears of biceps. If an anatomic repair of the cuff is possible, the area between the articular margin and the greater tuberosity will be decorticated to prepare a bleeding surface for reattachment of the tendon. The anchor selection will be based on the surgeon's personal preference. The number of anchors used will be recorded. After completion of suture anchor placement, braided sutures will be passed through the torn tendon as either mattress or simple sutures at the surgeon's discretion. Side-to-side sutures at the apex of the tear will be used as indicated. The type and number of sutures and suture anchors will be recorded

b. *Mini-open Repair *will follow arthroscopic examination of the glenohumeral joint and subacromial decompression. The arthroscope will be removed and the standard mini-open repair will be performed. A transverse or vertical skin incision at the lateral border of the acromion is made. Exposure of the cuff will be achieved by dissection of the deltoid fascia, and split of the deltoid from the level of the acromion distally for 4 cm. The edges of the tear are resected. The bone between the articular margin and the greater tuberosity is decorticated or a bone trough prepared at the surgeon's discretion. Suture anchors or transosseus sutures may be used along with side-to-side sutures. Details of technique will be recorded as above.

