##### Ensuring reproducibility and reliability of measurements of outcome

The reliability and validity of the primary outcome measures has been established in previous studies [48,50,71]. JOINTS Canada currently uses the WORC as a primary outcome measure in other studies involving patients with rotator cuff disease. Thus, research assistants are familiar with its administration. Study centres are also familiar with methods to minimize nonresponse and to ensure compliance with completing forms. Experienced research assistants at each of the participating sites will perform range of motion and strength measurements. Standardized methods of measuring range of motion [58,72-74], strength [15,75-78], and tear size will be provided in the study manual and are similar to techniques previously used in other JOINTS Canada studies. All participating JOINTS Canada investigators have agreed upon these standardized methods. All research assistants have been trained to use these methods. Secondary outcome measures are also standardized scales that are reliable and valid including: the ASES shoulder scale [51,79-81], the SF-12, and the Work Limitations Questionnaire (WL-26) [41].

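### The mini-open incision can reveal the arm to the research assistant who examines the shoulder, so the unqualified claim of assessor blinding is unsupported for motion, strength and Constant score

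*Protocol article*

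**What the plan says.** Under Control of biases through blinding, the protocol article concedes that surgeons cannot be blinded and then states that "the patient, the data collector, radiologist, and data analyst are blinded to group allocation for the duration of the study and data analysis". No outcome or visit is excepted. The abstract and the WORC section also call the research assistants blinded, as does the ROM section: "A blinded research assistant will assess active and passive measurements of range of motion (ROM").

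Planned trial interventions describes how each arm is operated on. The mini-open repair "will follow arthroscopic examination of the glenohumeral joint and subacromial decompression". The arthroscope is then removed, and "A transverse or vertical skin incision at the lateral border of the acromion is made", with a "split of the deltoid from the level of the acromion distally for 4 cm". The comparator is "an all-arthroscopic procedure where joint techniques and repair are both performed entirely thought the arthroscope".

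On who examines the shoulder, the section on reproducibility and reliability says: "Experienced research assistants at each of the participating sites will perform range of motion and strength measurements". For the Constant score, "the research assistant must work through each section with the patient". The ROM section applies to every post-operative assessment. The Strength and Constant sections give no schedule of their own, but the abstract places outcome measurement at 6 weeks and at 3, 6, 12 and 24 months after surgery.

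**The concern.** The mark that distinguishes the arms lies on the body part being examined. An assistant who has never been told the allocation may still see, on the shoulder to be measured, whether there is a lateral incision in addition to arthroscopic entry wounds. This route is separate from how the assignment is handled at randomization. It would remain if someone else obtained the assignment, and it applies to both designs because both use the same two operations.

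Goniometry, maximal-effort dynamometry and an assistant-led Constant score all depend partly on the examiner, through positioning, encouragement, end-point reading and scoring. Secondary objectives gives motion and strength particular weight because self-report is regarded as a poor indicator of cuff functionality. The Background also supplies a direction of expectation: it says faster recovery might be expected after the arthroscopic procedure, and it reports one comparative study with earlier return of motion in that group. If knowledge of the arm affected readings, a difference in these outcomes could partly reflect the examiner.

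**Working it through.** **Comparing the sections**

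1. *Skin entry.* Both arms have arthroscopic entry wounds, because the mini-open procedure begins with arthroscopy. Only the mini-open arm then has a lateral acromial skin incision. Its length is not stated; the 4 cm figure is the deltoid split.
2. *Examiner.* Research assistants measure motion and strength (reproducibility section) and work through the Constant score (Constant section). All three concern the operated shoulder.
3. *Design.* The interventions are the same in the conventional and expertise-based designs, so points 1 and 2 hold in both.
4. *Safeguard.* The article mentions no garment, dressing or other cover. It also does not say that the shoulder is bare.
5. *Stated reason.* The blinding section adds that bias is minimized because the primary outcome is self-reported. That does not reach outcomes measured by an examiner.

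Withholding the allocation is therefore not enough to deliver the stated blinding for these outcomes. Whether it is delivered depends on a step the article does not describe.

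**Illustration of size**

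The documents give no figure for how far knowledge of the arm might shift a reading, so this calculation rests on an assumption.

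Input from the Sample size section: 109 per group. It reproduces: 2 × (1.96 + 0.84)² × 450² × (1 − 0.55²) / 142.5² = 2 × 7.84 × 202,500 × 0.6975 / 20,306.25 = 109.07, stated as 109.

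Assumed input: a systematic shift of b SD in one direction between the groups, with no true treatment difference.

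For a two-sided 5% comparison of two means, the noncentrality is λ = b × √(109/2) = b × 7.382, and the false-positive rate is P(Z > 1.96 − λ) + P(Z < −1.96 − λ).

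| Assumed shift b | λ | False-positive rate |
|---|---|---|
| 0 | 0 | 0.050 |
| 0.10 SD | 0.738 | 0.114 |
| 0.15 SD | 1.107 | 0.198 |
| 0.20 SD | 1.476 | 0.315 |

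These rates are for each comparison and apply only if the average shift across all assessors and patients equals b. If assessors are effectively blinded, or their shifts cancel, the rate stays near 5%.

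**The case against.** The strongest objection is that silence is not evidence. This is a condensed article. The reproducibility section says that standardized methods for motion and strength are in the study manual and that the assistants are trained in them. What the patient wears during goniometry is the kind of detail a manual would hold. A reader might infer that the assessments are not blinded, or that nothing hides the incision. The documents support neither statement, and this part of the objection stands. What remains open is narrower: the article makes a positive, unqualified claim that its own surgical description puts in doubt.

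Second, the visible difference is not quantified. Both arms carry arthroscopic wounds, scar length is not given, and nothing shows how reliably a scar would identify the arm at 24 months. This also stands. The incision is a plausible cue whose strength is unknown.

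Third, a reader might carry over the strong procedural beliefs described in the Background to the examiners. Those passages concern surgeons. Nothing attributes a preference to research assistants, and a one-directional shift would need the assistants at seven centres to lean the same way on average. The illustration therefore cannot be read as an estimate.

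Fourth, a reader might extend the point to the radiologists, because only the mini-open description allows a bone trough or transosseous sutures. These are surgeon's options, suture anchors are permitted in both arms, and the documents do not show that imaging would reveal the arm. There is not enough to question radiologist blinding.

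Finally, motion, strength and the Constant score are secondary outcomes; the primary WORC is self-reported. That limits the weight of the point but does not remove it.

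**Conclusion.** The point holds in a limited form. As written, the statement that the data collector is blinded throughout is unsupported for motion, strength and the Constant score, in both designs: one arm has an additional incision on the shoulder being examined, and the article names no step to conceal it. It is a should-fix point about secondary outcomes.

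The size of any bias is unknown. The 11% to 31% range is arithmetic on an assumed one-directional shift of 0.1 to 0.2 SD, not something the documents establish.

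The conclusion rests on the incision being visible to the examiner, which the documents neither confirm nor exclude. It says nothing about whether the patient stays blinded; the patient can see the same incision, and covering the shoulder from the assessor does not change that.

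**What to change.** In the ROM, Strength and Constant sections, require that at every post-operative assessment both shoulders are covered with a T-shirt or opaque dressing before the assessor enters, and stay covered through motion, strength and Constant testing. In Control of biases through blinding, limit the assessor-blinding claim to assessments done under cover. If the study manual already requires covering, a sentence saying so in that section resolves the point.

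Two additions are optional: completing the questionnaires before the physical examination, and having the assessor record a guess of the arm at the end of the visit. The second measures blinding but does not protect it.

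The cost is a change to the manual and inexpensive garments or dressings, with no extra staff, visits or patients. The small drawback is that bony landmarks are palpated through cloth.

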##### Control of contamination and co-intervention

Patient intervention or crossovers within the expertise-based RCT are highly improbable. Crossovers from the conventional RCT may occur if surgeons feel a particular patient requires a specific type of surgery and, thus, are much more likely within this design. We will examine the records of all patients once surgery is completed to determine whether they received the assigned treatment. Crossovers will be recorded as major protocol violations. Surgical co-intervention is unlikely to occur at the time of surgery since we have specified in the eligibility criteria the concurrent procedures permitted. The biggest risk of co-intervention is if rehabilitation differs between the two groups. To avoid this, we have instituted a standardized rehabilitation protocol and will monitor adherence to this and the surgical protocol.

##### Ensuring reproducibility and reliability of measurements of outcome

The reliability and validity of the primary outcome measures has been established in previous studies [48,50,71]. JOINTS Canada currently uses the WORC as a primary outcome measure in other studies involving patients with rotator cuff disease. Thus, research assistants are familiar with its administration. Study centres are also familiar with methods to minimize nonresponse and to ensure compliance with completing forms. Experienced research assistants at each of the participating sites will perform range of motion and strength measurements. Standardized methods of measuring range of motion [58,72-74], strength [15,75-78], and tear size will be provided in the study manual and are similar to techniques previously used in other JOINTS Canada studies. All participating JOINTS Canada investigators have agreed upon these standardized methods. All research assistants have been trained to use these methods. Secondary outcome measures are also standardized scales that are reliable and valid including: the ASES shoulder scale [51,79-81], the SF-12, and the Work Limitations Questionnaire (WL-26) [41].

##### Control of biases relating to follow-up

The importance of complete follow-up to provide a valid estimate of outcomes in patients after rotator cuff surgery has been demonstrated [82]. We will use the following measures to ensure minimal loss to follow-up: 1) enrollment procedures will include the importance of compliance with follow-up and we will exclude patients who refuse 2-year follow-up; 2) study patients will supply, along with their own complete address and telephone information, similar contact information for 2 close associates; and 3) contact information will be updated at each study visit and by phone at 18 months. In addition, reminders of missed follow-up appointments are faxed to the research assistant who will immediately contact the patient to reschedule a missed appointment. Patients will be reimbursed for parking expenses associated with study. Patients who persist in noncompliance will be contact though telephone or internet survey for self-report outcome measures

